# Protocol summary

| Title | Study of population pharmacokinetics of benznidazole (BNZ) in children with Chagas disease |
| --- | --- |
| Duration | 24 months |
| Objective | To study the population pharmacokinetics of benznidazole in children with Chagas disease |
| Design | Phase I study in special populations (children). Population pharmacokinetics |
| Population | Ambulatory pediatric patients with Chagas disease |
| Sample size | Total N=50  Patients will be divided in 3 groups:   - Group 1: Patients receiving the first dose of BNZ (N=12) - Group 2: Patients in steady state of BNZ (N=26) - Group 3: Patients receiving the last dose of BNZ (N=12) |
| Selection Criteria | Children 2 to 12 years old with infection due to Trypanosome Cruzi (Chagas disease) |
| Inclusion Criteria | Children 2 to 14 year old under treatment with BNZ for Chagas disease.  Diagnosis of Chagas disease with at least 2 techniques (ELISA, hemagglutination or particle agglutination).  Informed consent provided by the parents and assentment provided by the patient. |
| Exclusion Criteria | Patients with hypersensitivity to BNZ.  Immunocompromised patients.  Altered liver or kidney function.  Pregnancy. |
| Treatment | Benznidazole 5-8 mg/kg/day p.o. in 2 daily doses for 60 days |
| Safety monitoring | Vital signs, adverse events, laboratory markers. |
| Samples for pharmacokinetics study | Samples per patient: 3 (sparse sampling)  Volume of blood per sample: 3ml |

# GENERAL INFORMATION

## Study Title

Study of population pharmacokinetics of benznidazole (BNZ) in children with chagas disease

# INTRODUCTION

##

## Background

Chagas disease is a parasitic infection caused by the parasite Trypanosome cruzi. The geographical distribution of this disease is wide, from the south of the USA to the south of Argentina, with endemic characteristics from the north of Mexico to the north of Argentina.^1^

The parasite that causes this disease can be transmitted by an arthropod vector, transfusions or mother to child transmission during pregnancy. Great progress has been achieved in the last years in the control of the transmission by the vector and by transfusion. Nevertheless, many challenges for the control of this infection still remain.

After the initial phase of the infection, which happens mainly in children and has a mortality of up to 10%, an asymptomatic phase ensues that will eventually lead to irreversible heart and /or intestinal tract damage in up to 30% of the patients many years after the initial infection.^1^

It is estimated that there are currently about 20 million people infected in Latin America, and that 200,000 new cases and 20,000 deaths due to complications of the disease happen every year.^1;2^ Most of the new infections happen in children, either by vector transmission or by vertical transmission. In Argentina, where 89% of the population lives in urban areas in particular in or around Buenos Aires, most of the patients infected with Chagas’ disease live in urban areas. Prevalence of Chagas’ disease in Buenos Aires has been estimated to be about 2%. Most new infections in urban areas are due to vertical transmission and occasionally due to blood transfusions. The transplacental route of transmission explains why most new cases in urban centers are detected in young children.

It has been shown that treatment of the infection in the acute phase is effective and carries a cure rate above 90%. Clinical trials have shown that the treatment of children in the quiescent phase leads to a positive therapeutic response.

New tools are being used to evaluate the response to the treatment such as PCR to detect parasite genome in blood and tissues and newer antigens for antibody tests. These advances have led to health authorities of Latin American countries and the World Health Organization to implement treatment programs of children with Chagas’ disease across central and Latin America.^3^

There are only 2 drugs currently available for the treatment of Chagas disease, nifurtimox and benznidazole.^1^

Benznidazole(N-benzyl-2-nitroimidazol-1-acetamide) is a nitroimidazol compound that was developed over 30 years ago.^4^ The mechanism of action of benznidazole is still not clear, but it has been shown to induce reductive stress leading to covalent modification of proteins and other macromolecules in the parasite.^1;5^ Another potential mechanism of action is the inhibition of the enzyme tripanotionine reductase, which leads to tripanotionine depletion, a molecule with important detoxification functions in the parasite T. cruzi.^4^ Benznidazole, and possibly its metabolites, like nifurtimox, induces the production of free radicals that can damage the parasite’s DNA, as well as inhibit RNA and protein synthesis. ^4;6^

Only 2 studies on the pharmacokinetics of benznidazole have been published to date, both in the 1970’s.

Benznidazole pharmacokinetics has been described as monocompartimental in healthy male adults.^7-9^ After a group of healthy male volunteers received 100 mg of benznidazole po, the plasmatic peak concentration of 2.2 – 2.8 mg/l was observed 3 – 4 hours post dose. The estimated half life was 12 hours, and the volume of distribution 0.56 l/kg.^8^ In a second study of multiple doses of benznidazole in Chagas patients, doses of 7 mg/kg produced plasma concentrations similar to those estimated based on the pharmacokinetic parameters obtained from the previous study.^9^ All patients reached steady state within 10 days of treatment with plasma concentrations between 5.4 – 16.4 mg/l (estimated required plasma concentration to kill the parasite: 3 – 6 mg/l).

Benznidazole is eliminated by the liver, with less than 20% excreted unchanged by the kidney. Protein binding is moderate (40%), and distribution into tissues is good, including central nervous system, liver, and red blood cells. There are virtually no studies on the metabolism of benznidazole in humans, and very little and outdated information is available from animal studies.

Benznidazole, and other drugs used for the treatment of Chagas disease have never been adequately studied in the pediatric population.^10;11^ Also, there is no appropriate formulation for use of this drug in the pediatric population (liquid formulation), which many times forces health care providers to recur to pill fractionation, a methodology fraught with difficulties and risks.^12;13^

In response to this dearth of information in the pediatric population, the Scientific Working Group on Chagas Disease, TDR, WHO/PAHO has signaled the study of the pharmacokinetics of benznidazole and nifurtimox in children as a research priority.

Pharmacokinetic studies have traditionally involved a limited number of patients, usually healthy volunteers. Pharmacokinetic profile of the studied drug would usually be characterized extensively in each individual participant, which requires a large number of samples to be obtained. The requirement for extensive sampling makes traditional pharmacokinetics studies very difficult to perform in pediatric populations due to ethical and logistical limitations (e.g. blood volume restrictions, inordinate number of punctures, etc).

In the last few decades, a new approach to pharmacokinetics, population pharmacokinetics, has gained momentum as the method of choice when studying vulnerable populations such as children. This method changes the focus away from the complete estimation of the pharmacokinetics parameters of each individual participant towards the estimation of the parameters (and its variability) in the whole population. In order to estimate the pharmacokinetics of a drug from a population perspective, a larger number of individuals is required to participate, but the amount of samples per individual is greatly reduced (to as little as 2 samples in some designs). This milder burden on the individual patient makes population pharmacokinetics the method of choice for studies in the pediatric population.

This method has been recommended by the FDA and EMEA as the standard method for pharmacokinetic studies in children.^14-16^

Given the absolute absence of data on the pharmacokinetics of benznidazole in the pediatric population, we propose to carry out a population pharmacokinetics study of this drug in children receiving this drug for the treatment of Chagas disease.

# OBJEcTIVe

To study the pharmacokinetics of benznidazole in children with Chagas’ disease.

# study design

## Study type

Population pharmacokinetics study.

Observational prospective study in especial populations (children).

## Population

### Selection criteria

Children 2–12 years old, with Chagas’ disease*.*

### Inclusion criteria

- Children 2 – 12 years old, both sexes, with a diagnosis of Chagas’ disease and eligible for treatment with benznidazole, as per current treatment protocols.
  - Chagas’ disease diagnostic criteria: At least 2 positive serological tests for *Trypanosoma cruzi* infection técnicas serológicas reactivas (ELISA, Hemmoagglutination and particle agglutination tests).
- Informed consent signed by the parents and assentment of the patient.

### Exclusion Criteria

- Patients with a history of hypersensitivity to benznidazole or any of the drug excipients.
- Immunocompromised patients (Clinical history compatible with HIV infection, cancer, primary immunodeficiencies or prolonged treatment with corticosteroids or other immunosuppressants)
- Altered hepatic function (increase in AST/ALT x3 or billirubin x3).
- Altered renal function (increase in creatinine x3).
- Pregnancy

### Criteria for withdrawal from the study

- Non-compliance with treatment plan
- Severe drug reaction potentially attributable to benznidazole
- Any situation that may put the safety of the patient at risk, according to the judgment of the researchers or attending physicians.

#

# research plan

## General overview of the study

Pretreatment period

(Days -30-0)

Treatment period (Days 1- 60)

Post-Treatment Period

(Days 61-63**)**

Clinical history, physical exam, CBC, Chagas serology, Liver and kidney function tests (pretreatment, days 0, 7, 30 and 60)

**Group 1**: N=12

Patients taking the first dose

(Sampling windows:

a) 0 - 2 hs;

b) 2 - 6 hs

c) 6 - 12 hs

post dose)

**Group 2**: N=26

Patients in steady state (Days 3 - 59)

(Sampling windows:

1. through – before next dose
2. 0 - 2 hs post dose
3. 2 - 6 hs post dose)

**Group 3**: N=12

Patients taking the last dose (Days 61 - 63)

(Sampling windows: a) 12 - 18 hs

b) 18 - 24 hs

c) 24 - 36 hs

post dose)

Safety monitoring and adverse events recording

**Day 0**

**Day 30**

**Day 60**

**Day 7**

Children 2-12yo with Chagas’ disease under treatment with benznidazole,5-8 mg/kg/d bid po

Routine visits for treatment and follow up

## Patient recruitment

Patients eligible for the study will be recruited at the Parasitology Division, Children’s Hospital of Buenos Aires, Buenos Aires, Argentina, where these patients are routinely treated and followed up. Recruitment will be carried out by the treating pediatrician and principal investigator, [name].

## Study duration

The recruitment phase of the study will take an estimated 24 months.

## Data collection

Information on clinical examination, weight, height, cardiological evaluation, and clinical biochemistry results will be collected. These studies are done routinely in children with Chagas’ disease under treatment with benznidazole.

## Treatment

The patients will receive, as per routine treatment protocol of Chagas disease, Benznidazole (RADANIL®, Roche). Dose: 5-8 mg/kg/d, bid, PO for 60 days. The patients are usually treated in an outpatient setting.

Benznidazole will be provided by the Argentine National Ministry of Health, for free. The patients will be given enough benznidazole for 1 month of treatment plus 5 days. Pill counts will be carried out at the day 30 visit, when enough benznidazole to complete the remaining of the treatment will be given to the patient’s family. Pill counts will be carried out again at the end of the treatment period.

The patients parents will be given a treatment diary to complete during the treatment period with daily times of ingestion of the medication and any events that they think might be related to the treatment.

All concomitant medications will be registered in the patient’s chart. There is no available information to date neither on the metabolism of benznidazole, nor on potential drug interactions.

## Follow up

Patients will be followed according to the usual management protocol of children with Chagas’ disease, at the ambulatory clinic of the Division of Parasitology, Children’s Hospital of Buenos Aires.

Patients will be seen at the clinic at diagnosis, 7, 30 and 60 days after the start of the treatment. Clinical examination and laboratory studies will be performed at each visit, including CBC, liver and renal function tests and Chagas serology.

Parents will be instructed to report adverse events potentially related to the treatment.

Patients will be seen 3 months after the treatment period is completed, and every 6 months after that. Serology for Chagas’ disease will be performed at each visit.

All adverse events will be immediately reported to the pharmacovigilance division of the ANMAT (Argentine National Administration of Medications and Medical Technology).

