## Overview of diagnostic studies

| Visit | 0 | 1 | 2 | 3 | 4 |
| --- | --- | --- | --- | --- | --- |
| Time | 0 | 7 d | 1m | 2m | posttreatment |
| Informed consent | X |  |  |  |  |
| Clinical history | X | X | X | X | X |
| Physical exam | X | X | X | X | X |
| Chagas’ serology | X | X | X | X | X |
| CBC | X | X | X | X |  |
| Liver enzymes | X | X | X | X |  |
| Creatinine | X | X | X | X |  |
| Cardiological exam | X |  |  |  |  |
| Adverse event evaluation |  | X | X | X | X |
| Drug measurements (may not coincide with clinical visits) |  | X | X | X | X |

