# Adverse drug events

Every adverse event, whether related to benznidazole or not, will be registered and notified to the pharmacovigilance division of the ANMAT, as well as the Teaching and Research Committee of the Children’s Hospital of Buenos Aires.

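### The parent diary and the parent reporting instruction ask for fewer adverse events than the protocol's own rules require to be registered and reported

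*Protocol*

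**What the plan says.** Two places in the protocol set a broad rule. Section 10 (Adverse drug events): "Every adverse event, whether related to benznidazole or not, will be registered and notified". Section 7.6 (Follow up): "All adverse events will be immediately reported to the pharmacovigilance division of the ANMAT". Neither limits the duty by cause.

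Two places tell parents what to supply. Section 7.6: "Parents will be instructed to report adverse events potentially related to the treatment". Section 7.5 (Treatment) gives them a diary for daily dosing times and "any events that they think might be related to the treatment".

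Staff also collect events directly. The visit table in section 7.8 (Overview of diagnostic studies) has a row "Adverse event evaluation", marked at visits 1 to 4 (7 days, 1 month, 2 months and post-treatment), with clinical history and physical examination at the same visits. On timing, section 7.6 says: "Patients will be seen at the clinic at diagnosis, 7, 30 and 60 days after the start of the treatment". It adds: "Clinical examination and laboratory studies will be performed at each visit, including CBC, liver and renal function tests". The protocol summary lists adverse events as part of safety monitoring.

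**The concern.** An all-events rule can be met only for events that staff come to know about. Between visits the parents are the main source, and the protocol asks them to sort events by cause before writing them down or reporting them. The diary wording is the clearer evidence, because it makes the judgement explicitly the parents' own. The instruction in 7.6 does not say who judges.

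Parents are poorly placed to make that judgement here. The Background says that the drug has not been properly studied in children, and section 7.5 says that nothing is known about its interactions. If the protocol cannot say which events are related, a parent's opinion is a weak basis for leaving one out, and an unexpected reaction is the kind most easily put down to something else. What is at stake is the completeness of the safety record. An event that is never recorded cannot be recovered at the analysis stage, so this is a matter for the collection rules and not for an analysis plan.

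**Working it through.** The protocol states no adverse event rate, so there is no figure to reproduce. The check compares the texts and works out the time exposed.

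**1. Scope of each source**

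| Place | Who acts | Scope |
| --- | --- | --- |
| Section 10 | Study staff | Every event, any cause |
| Section 7.6, reporting sentence | Study staff | All events, immediately |
| Section 7.6, parent instruction | Parents | Possibly related events only; judge not named |
| Section 7.5, diary | Parents | Only events the parents suspect are related |
| Section 7.8, visits 1 to 4 | Study staff | No causality limit stated |

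Both parent sources are narrower than both staff rules. Section 7.6 holds a narrow instruction and an all-events rule side by side.

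**2. Time between scheduled on-treatment visits** (days 7, 30 and 60, section 7.6)

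- Day 7 to day 30: 30 − 7 = 23 days.
- Day 30 to day 60: 60 − 30 = 30 days.
- Together: 23 + 30 = 53 of the 60 treatment days.

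**3. Which events are exposed.** An event still present at a visit, or one that leaves a laboratory trace, can be found by examination or blood tests whatever the parents think. An event that begins and ends inside a gap may leave no such sign. If the parents thought it unrelated, the diary did not ask for it, and its capture depends on recall at the next evaluation.

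**4. Timeliness.** If the event is recalled at the next visit, staff may first hear of it up to 23 or 30 days after it began. The protocol does not say whether immediate reporting runs from the event or from the moment staff learn of it. On the first reading the rule cannot be met for such an event. On the second it is met formally, but late.

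**5. Can the loss be sized?** Let f be the share of events that parents would judge unrelated, and r the share of those that visits recover. Then

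share of events captured = 1 − f(1 − r).

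The protocol gives neither quantity. With assumed values:

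| f | r = 0 | r = 0.5 | r = 1 |
| --- | --- | --- | --- |
| 20% | 80% | 90% | 100% |
| 60% | 40% | 70% | 100% |

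The result runs from a large loss to none, depending on values that the documents do not fix. These are shares of events, not of children: a child with one omitted and one recorded event still counts as having had an event. The table shows only that no single figure can be defended.

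**The case against.** The strongest reply is that the two sets of rules govern different things. Section 10 says what the study registers; 7.5 and 7.6 say what parents are prompted to volunteer. Staff can follow both by registering every event they learn of, and they ask again at visits 1 to 4 with no causality limit. This stands in large part. It means that capture as a whole is not filtered by parents, although a reader of 7.5 and 7.6 alone might infer that it is. It does not cover the transient event that parents discount and later forget, and no text says that the visit evaluation must go beyond the diary.

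A second reply is that children may be seen between clinical visits. Group 2 (26 of the 50 children) is sampled on days 3 to 59, and the visit table allows drug measurements away from clinical visits. This also stands: the gaps cannot be described as free of contact. But these contacts are not assured, since section 7.7 prefers to combine sampling with routine blood draws, and no adverse event evaluation is scheduled for them.

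Third, the wording given to parents sets a low threshold, so many events would be reported anyway. That is fair, and it is one reason why the loss may be small.

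Fourth, asking for everything would send more events to the regulator. That is true, but sections 7.6 and 10 already require those notifications.

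**Conclusion.** The mismatch is real and can be read directly from the text: the diary and the parent instruction are narrower than the registration and reporting rules they should feed. The practical exposure is limited to events that arise and resolve in the 23-day or 30-day gap and that parents consider unrelated. These may be missed, or may reach staff too late for immediate reporting.

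A reader might go further and infer that adverse event rates will be understated. The documents do not support that. Any error from this source would be towards too few events, but its size depends on parental judgement and on recovery at visits, neither of which is given, and it is zero if visits recover everything. Nor is an adverse event rate named as an objective or used to set the sample size. The objective is pharmacokinetic and those estimates are unaffected. The point concerns the completeness and timeliness of the safety record, and it assumes that parents follow the diary and the instruction as written.

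**What to change.** Reword sections 7.5 and 7.6 so that parents record in the diary, and report, every new symptom or illness with its start and stop dates, whatever they believe caused it. State that the investigator reviews the diary with the family at each visit and assigns causality. Section 10 and the all-events sentence in 7.6 can stay as they are.

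The change is to the protocol wording, the diary form and the instructions to parents. It adds no visit or blood sample and leaves treatment unchanged. The running cost is more entries to review and more events to notify. The protocol does not allow that increase to be estimated, and it should not be assumed trivial, but it is work that section 10 already requires. The change should be made before enrolment, because events left out of completed diaries may not be recoverable later.

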## Sample obtention for pharmacokinetics

The patients enrolled in the study will be divided in 3 groups:

- Group 1: Patients receiving the first dose of benznidazole (N=12; Sampling windows: a=0-2hs; b=2-6hs; c=6-12hs post dose).
- Group 2: Patients in steady state phase (at least after 3 days of treatment; Days 3-59).(N=26; sampling windows: a=through–before next dose; b=0-2hs; c=2-6hs post dose).
- Group 3: Patients receiving the last dose of benznidazole (Days 61-63).(N=12; Sampling windows: a=12-18hs; b=18-24hs; c=24-36hs post dose).

Time of drug administration and blood extraction will be registered in a form. Extraction times will be distributed across the sampling windows (see 7.1), and taking into account, to the extent possible, patient availability and preferences.

Blood extraction will done using a butterfly needle, with previous application of anaesthetic cream. Blood extractions will be done, whenever possible, within the context of other routine blood extractions required for the clinical follow up of the patient.

Samples will be stored in the fridge until extraction (less than 48 hs).

Benznidazole extraction and measurement: Benznidazole will be extracted and measured (by HPLC) according to published protocols.^17-21^

### Group 1: Patients receiving the first dose of benznidazole

Number of patients: 12.

Number of blood extractions per patient: 3. The first extraction between 0 and 2 hours, the second extraction between 2 and 6 hours and the third extraction between 6 and 12 hours post dose.

Blood volume per extraction: 3ml.

Minimal interval between samples: 1 hour.

